### Sample size

The sample size is calculated based on data on adult female *Aedes* mosquitoes collected using mechanical aspirators (15 min outdoors and indoors each) from a case-control study in nearby districts during 2016 and 2017. The mean capture was 0.78 mosquito per house (indoors + outdoors). At minimum, 34 clusters are needed to detect a 90% difference in adult female mosquitoes per house with 90% statistical power and a two-sided significance level (α) of 0.05 assuming 10 households are visited three times each after the intervention begins and a between-cluster coefficient of variation of 0.33. Sample size methods for cluster-randomized trials were used [49], as implemented in the ‘clustersampsi’ add-on to Stata® statistical software [50]. The existing data were over-dispersed relative to a Poisson distribution; therefore, to represent a negative binomial distribution with a dispersion parameter (α, or 1/*k*) of 2.03 estimated from the same data, the ‘means’ option was used, with the variance in each arm equal to the mean plus the square of the mean times α [51]. The clusters are split equally between the strata (Khon Kaen and Roi Et). To provide an equal number of clusters in each arm, one extra cluster is added per stratum, i.e., 18 clusters per stratum (city) and 9 clusters per arm in each stratum.

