### Interventions

Following approximately 10–12 months of baseline data collections, household interventions will begin in the selected intervention clusters (Fig. 2). The intervention specifically targets mosquito immature stages by applying a mixture of pyriproxyfen and spinosad to all permanent household containers, whether indoor or outdoor, found to contain water up to a 10-m perimeter from the house. Pyriproxyfen is an insect growth regulator (insect juvenile hormone analog) that is active against pupal stages, resulting in the inhibition of adult development (preventing emergence). It has low mammal toxicity and is recommended by WHO for vector control [52]. Spinosad is a natural insecticide produced by the soil bacterium *Saccharopolyspora spinosa*. It has a neurotoxic mode of action in insects, but with low mammal toxicity, and it is also recommended by WHO [52]. The doses recommended by WHO for *Aedes* immature mosquito control are 0.01 mg/L active ingredient (a.i.) pyriproxyfen (applied as a 0.5% granule formulation) and 0.1–0.5 mg/L a.i. spinosad (also a 0.5% granule formulation) [45, 53]. Both pyriproxyfen and spinosad have also been assessed and approved by WHO for use in drinking water containers [54, 55]. The reasons for selecting this novel intervention are that the combination of pyriproxyfen and spinosad has not yet been tested in a national dengue vector control program; that it should be effective, easy, and practical to use for national control authorities; and that its combined use reduces the risk of resistance development. The interventions will be implemented by project staff from the Ministry of Public Health, thereby ensuring adherence to intervention protocols.

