#### Statistical methods

For the entomological endpoints, clustering will be taken into account by analyzing summary measures at the level of cluster. The MEI, expressed as a continuous variable, is a characteristic of individual people, not houses, and its main analysis will be by multivariable multilevel modeling with three levels: cluster, individuals within clusters, and measurements (time points) within individuals. As before, the exposure of main interest will be the arm of the trial (intervention versus control). Individual-level covariates will include age (5–14, 15–25, and > 25 years) and sex. Vector control intervention (i.e., arm of the trial) will be used as a covariate at cluster level. Other cluster-level covariates may include abiotic factors (such as rainfall, temperature, and relative humidity) and population density. An additional analysis of MEI will be by summary measures, as for the other endpoints.

For all analyses of summary measures, the arm of the trial will be the exposure of main interest and will be included in regression models as a dichotomous variable. Stratification will be represented by including a dichotomous variable for city. Finally, the baseline value of each outcome, summarized over the pre-intervention rounds, will be included as a categorical variable, with the expectation that this will reduce the residual error.

For each outcome variable, the response variable for the main analysis will be the aggregate value, for each cluster, of the post-baseline measurements. However, for the primary endpoint (AI), an additional analysis will include the values at each post-baseline time point for each cluster, and will include an interaction between the arm of the trial and the time point, with the aim of identifying a possibly waning effect of the interventions.

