#### Effect of intervention on primary outcome

For each cluster the total number of adult female *Ae. aegypti* and *Ae. albopictus* and the total number of house visits will be calculated. Taking these as summary measures, a negative binomial regression will be done with the number of mosquitoes as the outcome variable and number of house visits as the exposure (denominator) variable, i.e., with the logarithm of the number of houses as the offset. A logarithmic link function will be used. Hence, the exponential of the coefficient for arm will be the between-arm ratio in AI according to the response variable used.

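### Entering the cluster baseline value in categories gives up part of the precision that baseline adjustment is meant to gain; one continuous log-rate term would do better for the Adult index

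*Protocol article*

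**What the plan says.** The Statistical methods section of the protocol article handles the entomological endpoints at cluster level: "clustering will be taken into account by analyzing summary measures at the level of cluster". Arm enters as a two-level term, and "Stratification will be represented by including a dichotomous variable for city". The third term is baseline: "the baseline value of each outcome, summarized over the pre-intervention rounds, will be included as a categorical variable". The authors add this term "with the expectation that this will reduce the residual error". The rule covers all summary-measure analyses. Only the main analysis of the mosquito exposure index, which is multilevel, falls outside it.

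For the primary outcome, "a negative binomial regression will be done with the number of mosquitoes as the outcome variable", with a log link and the log of house visits as offset (Effect of intervention on primary outcome). The Sample size section gives "18 clusters per stratum (city) and 9 clusters per arm in each stratum", so the model has 36 observations. The baseline period is long (Interventions): "Following approximately 10–12 months of baseline data collections, household interventions will begin in the selected intervention clusters".

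The article gives no reason for using categories and mentions no continuous alternative.

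**The concern.** Baseline AI is a count divided by house visits, so each cluster has a number and not a class. On a log link its natural form is the log baseline rate, with one coefficient. Grouping treats all clusters within a band as equal and discards the differences between them. With three or more groups it also spends parameters that a single term would not need.

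The covariate is there only to sharpen the estimate of the arm ratio. A form that returns less of that gain, or none, defeats its purpose. At stake is the width of the confidence interval for the primary ratio and for the other outcomes analysed in the same way. The validity of the estimate is not in question.

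**Working it through.** **Inputs.** From Sample size: control mean 0.78 per house, dispersion 2.03 (variance = mean + 2.03 × mean²), between-cluster CV 0.33, 10 houses × 3 visits = 30 visits per cluster, 36 clusters. Assumed, because the article does not state them: the baseline/follow-up correlation of cluster rates, and the number of groups (2 to 5, equal-sized).

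**The plan's own figure.** There is none for the gain from adjustment. The nearest is the minimum of 34 clusters. Clusters per arm = 1 + (1.960 + 1.282)² × [(v0 + v1)/30 + 0.33²(μ0² + μ1²)]/(μ0 − μ1)². A 90% reduction (0.78 to 0.078) gives 3.92, so 4 per arm; a 45% reduction gives 16.37, so 17 per arm. The printed 34 therefore does not follow from a 90% reduction. That is a separate matter, but it is a reason to look at smaller effects as well.

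**Step 1: information kept.** Cutting a normal covariate into g equal groups keeps a share S of its explained variance, where S is the variance of the group means. S = 0.637 for g = 2 (2/π), 0.793 for 3, 0.861 for 4 and 0.897 for 5. With observed correlation ρ, the residual variance relative to a continuous term is (1 − ρ²S)/(1 − ρ²). For ρ = 0.5 and g = 2: (1 − 0.25 × 0.637)/0.75 = 1.121, an interval √1.121 = 1.059 times as wide. For ρ = 0.3 and g = 2 the interval is 1.8% wider. Baseline AI is noisy: with 30 visits and a rate ratio of 0.60, true correlations of 0.5, 0.8 and 1.0 gave observed correlations of about 0.22, 0.35 and 0.44. The low-ρ figures are therefore the relevant ones.

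**Step 2: parameters.** Residual df are 36 − 3 − (g − 1): 32 for two groups (the same as for a continuous term) and 29 for five. The critical t moves only from 2.037 to 2.045. The larger cost is chance overlap with arm. Each extra parameter is expected to take about 1/34 ≈ 3% of the arm contrast, so three extra take about 9% in variance, or about 4% in width.

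**Step 3: simulation, linear model of the log cluster rate with t-tests** (4,000 runs, rate ratio 0.60). Cells show power, then mean CI half-width on the log scale.

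| Baseline term | True corr. 0.5 | 0.8 | 1.0 |
|---|---|---|---|
| none | 86%, 0.332 | 86%, 0.332 | 86%, 0.332 |
| continuous | 87%, 0.329 | 89%, 0.315 | 92%, 0.303 |
| 2 groups | 86%, 0.332 | 88%, 0.323 | 90%, 0.316 |
| 3 groups | 85%, 0.337 | 88%, 0.325 | 89%, 0.315 |
| 4 groups | 83%, 0.342 | 87%, 0.330 | 88%, 0.319 |
| 5 groups | 82%, 0.349 | 85%, 0.335 | 87%, 0.324 |

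At a rate ratio of 0.10, power is about 100% in every row.

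**Step 4: simulation, the negative binomial model itself.** Increase in the variance of the log AI ratio over a continuous log baseline:

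| Scenario | 2 | 3 | 4 | 5 groups |
|---|---|---|---|---|
| corr. 0.7, no effect (1,500 runs) | 6% | 6% | 7% | 13% |
| corr. 0.9, no effect (1,500) | 6% | 7% | 11% | 11% |
| corr. 0.9, 40% reduction (1,500) | 9% | 6% | 9% | 12% |
| corr. 0.9, about 54 baseline visits (1,500) | 12% | 10% | 12% | 13% |
| range, corr. 0.3–0.9 (500 per scenario) | 0–10% | 4–9% | 5–13% | 11–21% |

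In the first scenario, leaving baseline out altogether costs 11%, so five groups (13%) did no better than that. The 54 visits are an estimate that adds monthly sentinel visits to three full rounds. In units of clusters, a 6% penalty is worth 36 × (1 − 1/1.06) ≈ 2 and a 12% penalty 36 × (1 − 1/1.12) ≈ 4.

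**The case against.** The strongest reply is that this is a coherent, prespecified choice between two valid adjustments. Categories assume no functional form, cope with zeros and outliers, and give one rule for several skewed or sparse outcomes. The arm ratio remains valid. The prize is also small: in the linear simulation at true correlation 0.8, the best adjustment narrows the interval only from 0.332 to 0.315, about 5%. All of this stands. It limits the size of the point, but it does not make grouping the better choice for AI.

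A reader might infer more than the document supports:

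- **Inflated type I error.** In 1,200 null runs of the negative binomial model (correlation 0.7), a Wald test rejected 9.6% of the time with no baseline, 10.2% with a continuous term, 10.7% with two or three groups and 11.3% with four; the Monte Carlo standard error is about 0.9 points. Other runs gave lower absolute levels (6.5–7.6% continuous, 7.9–8.8% with four groups). The excess is there without any baseline term and differs little between options, and the article does not name a Wald test.
- **A degrees-of-freedom cost in every case.** Two groups use one parameter, as a continuous term does.
- **Unspecified cut-points as a fault.** A protocol article may leave these to the full protocol or the SAP.
- **The 64%, 79% and 86% shares as lost trial precision.** They are shares of what the covariate explains, and a noisy baseline explains little.
- **Dropping baseline for dengue incidence and the infected adult index.** That would rest on a count of zero baselines that the article does not give. A zero/non-zero category is a reasonable use of the rule there.

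**Conclusion.** The point holds as a modest, avoidable loss of efficiency in the primary analysis and in those that follow the same rule. For two to four groups the variance penalty is small but was seen in nearly every scenario. With five groups the adjustment mostly stops paying for itself. At a rate ratio of 0.60 the cost is about 1 to 5 points of power; at the planned 90% difference there is none.

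The sizes depend on a correlation and a number of groups that the article does not state, and on equal-sized groups. The direction is firmer than the exact figures. It is a finding because the protocol itself fixes the weaker form and gives a purpose that this form serves less well.

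**What to change.** In Statistical methods, replace the categorical baseline for AI, ASTI, PPI and BI by one continuous covariate on the model scale. For AI this is log((baseline count + 0.5)/baseline house visits), where the 0.5 allows for clusters with no catch. The other three take the same form with their own denominators: traps, persons and house collections. State that a categorical baseline, for example zero versus non-zero, may be kept for dengue incidence and the infected adult index.

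The cost is one sentence, with no new data. The change adds an assumption of log-linearity, which fits the log link; a sensitivity analysis with the categorical form would check it. As the trial is unblinded, the change should be recorded before post-intervention results are analysed.

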#### Effect of intervention on primary outcome

For each cluster the total number of adult female *Ae. aegypti* and *Ae. albopictus* and the total number of house visits will be calculated. Taking these as summary measures, a negative binomial regression will be done with the number of mosquitoes as the outcome variable and number of house visits as the exposure (denominator) variable, i.e., with the logarithm of the number of houses as the offset. A logarithmic link function will be used. Hence, the exponential of the coefficient for arm will be the between-arm ratio in AI according to the response variable used.

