### Outcomes

The primary outcome is the Adult index (AI, the number of female adult *Ae. aegypti* and *Ae. albopictus* collected per house) (Table 1). The AI is based on combined indoor and outdoor collections using mechanical, battery-powered aspirators for 30 min (2 × 15 min) by staff of the local public health departments. The AI for each species will be recorded separately, although the general expectation is to find a predominance of *Ae. aegypti* in all urbanized clusters.

**Table 1 Tab1:** Primary and secondary outcome measures and other entomological indices

Outcome	No.	Index abbreviation	Index name	Description	Unit	Frequency of data collection	Details
Primary outcome	1	AI	Adult index	Number of female adult *Ae. aegypti* and *Ae. albopictus* per house collected both indoors and outdoors	No./house	Once every 4 months in all households (HHs) and once every month in 3 HHs per cluster (the same ones each time)	Adult collections using a mechanical battery-powered aspirator for 30 min per house (indoors and outdoors)
Secondary outcomes	2	DIR	Dengue incidence rate	Number of confirmed dengue cases/observation days of household populations	Rate	Weekly	VHVs detect fever cases. Hospital and project staff collect blood samples
	3	MEI	Mosquito exposure index	(1) Differential optical density for antibodies to *Ae. aegypti* saliva (2) Proportion above the immune threshold for this assay	(1) Number (2) %	Once every 4 months in all HHs and once every month in 3 HHs per cluster (the same HH as for the AI)	Recurring blood spots from two persons per HH taken on filter paper. IgG antibody response (positive or negative) to the *Ae. aegypti* Nterm-34 kDa salivary peptide
	4	IAI	Infected adult index	Number of DENV-infected adult female *Ae. aegypti* and *Ae. albopictus*	No./house	Once every 4 months in all HHs and once every month in 3 HHs per cluster	Based on adult mosquito collections indoors using a mechanical battery-powered aspirator for 15 min per house and DENV detection in individual mosquitoes
	5	ASTI	Adult sticky trap index	Total number of *Ae. aegypti* and *Ae. albopictus* females collected by sticky traps per month	No./trap/month	7 consecutive days per month	Adult mosquitoes collected by sticky traps baited with hay infusion for 7 days every month

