#### Entomological collections

Mosquito collections will be carried out in all participating households *every 4 months* (Fig. 2). In addition, *monthly* collections will be done in the three sentinel households per cluster, using the same households as those used for the blood spot collections for logistical reasons. The following data will be recorded from each household: number of total containers (potential breeding sites, wet or dry), number of containers with water, number of mosquito positive and negative containers (any species), container type, and location (indoors/outdoors) using defined criteria. Mosquito larvae will be collected from all positive containers using a standard larval dipper to determine species composition (both *Ae. aegypti* and *Ae. albopictus* will be identified and recorded). Pupae will be collected using the pupal/demographic survey method [19] and the “five-sweep” net procedure for very large containers [61].

Adult mosquitoes will be collected for 15 min indoors (in living rooms, bedrooms, etc.) and 15 min outdoors (among man-made articles, vegetation, etc.) from each household using a Prokopack mechanical aspirator [62]. Adult mosquitoes will also be collected using stationary sticky lure gravid *Aedes* traps [63] placed in a location where mosquitoes are abundant (based on householders’ knowledge) at four selected households for *7 consecutive days every month*. Specimens will be taken to a laboratory for sorting and identification using a stereomicroscope and morphological keys [64, 65]. Larvae (separated by species) and pupae (separated by species and sex) will be stored in absolute 99.5% ethanol in labeled 1.5-mL Eppendorf® tubes. Blood digestion status (fed or not fed) of female mosquitoes will be determined by external examination of abdomens. Adult mosquitoes (separated by species and sex) will be stored individually in absolute 99.5% ethanol in 1.5-mL labeled Eppendorf tubes. All specimens will be transported to Khon Kaen University and stored at –80 °C until further processing.

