### Analysis

#### Index calculations

For all outcomes, baseline measurements will start in the second half of 2017. Post-intervention measurements will start in the second half of 2018. The following indices or rates will be used:*Adult index (AI)*. Number of adult female *Ae. aegypti* and *Ae. albopictus* per house (combined species) collected both indoors and outdoors for 15 min at each location (30 min total collection time), using a battery-driven mechanical aspirator. Collections will occur once every 4 months in all households and once every month in three repeat sentinel households per cluster*Dengue incidence rate (DIR)*. Number of confirmed dengue cases divided by observation days of household populations. All household members with a fever will be identified during weekly VHV visits in participating households. Confirmed dengue cases are those febrile patients with a rapid diagnostic test (RDT) positive for NS1, IgM, IgG, or combinations thereof and a subsequent positive laboratory RT-PCR*Mosquito exposure index (MEI)*. ΔOD in IgG antibodies to *Ae. aegypti* Nterm-34 kDa salivary peptide using immunoassays, within the sampling scheme described above. Also the proportion for whom this differential optical density is above the TR defined above*Infected adult index (IAI)*. Number of DENV-infected adult female *Ae. aegypti* and *Ae. albopictus* per house (combined species) collected both indoors and outdoors for 15 min each, using a battery-driven mechanical aspirator. DENV presence will be confirmed by real-time RT-PCR as described above*Adult sticky trap index (ASTI)*. Number of adult female *Ae. aegypti* and *Ae. albopictus* (combined species) collected each month using one sticky trap per house baited with an oviposition attractant hay infusion. Collections will be done in three selected households for 7 consecutive days per month*Pupae per person index (PPI)*. Total number of *Aedes* pupae collected in participating households divided by the number of persons in that household. Collections will be done once every 4 months in all households and once every month in three repeat sentinel households per cluster*Breteau index (BI)*. Number of immature *Aedes* positive containers per 100 houses measured at the cluster level. Collections will be done once every 4 months in all households and once every month in three repeat sentinel households per cluster

Other indices are described in Table 1.

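### The primary model names house visits as its exposure but gives log(number of houses) as the offset, and the pooled Adult index is weighted towards three sentinel houses

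*Protocol article*

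**What the plan says.** All references are to the protocol article.

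- **Effect of intervention on primary outcome:** for each cluster the mosquitoes and "the total number of house visits will be calculated". The negative binomial model then takes "number of house visits as the exposure (denominator) variable, i.e., with the logarithm of the number of houses as the offset".
- **Statistical methods:** "the response variable for the main analysis will be the aggregate value, for each cluster, of the post-baseline measurements".
- **Index calculations**, under the AI: "Collections will occur once every 4 months in all households and once every month in three repeat sentinel households per cluster". Table 1 gives the same two frequencies and says that the monthly houses stay the same.
- **Entomological collections:** the monthly "collections will be done in the three sentinel households per cluster" come on top of the 4-monthly rounds. They use the blood-spot houses, for logistical reasons.
- **Sample size:** the calculation was made "assuming 10 households are visited three times each after the intervention begins". It does not mention the monthly visits.
- **Analysis populations:** a cluster that leaves the trial early stays in the primary analysis if it has any primary-outcome data.

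**The concern.** There are two points, the first being the firmer.

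**Offset.** One sentence gives two denominators as if they were the same. With log(visits), the model estimates mosquitoes per house visit, which is the AI. With log(houses), it estimates mosquitoes per house over however many visits took place, so a cluster with fewer visits looks less infested. The plan keeps partly observed clusters, so unequal visit counts are foreseen.

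**Visits that enter the index.** Nothing limits the primary AI to the all-house rounds or gives the ten houses equal weight. Read literally, the three sentinel houses dominate the visit count, and the analysed data set differs from the ten-by-three layout used for the sample size. The ten houses are those nearest a randomly chosen grid cell; the article does not say how the three were picked from them.

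**Working it through.** **1. Offset.** Let a cluster have H houses, n visits and a mean of λ mosquitoes per visit, so the expected total is nλ. An offset of log n gives a fitted rate of λ. An offset of log H gives nλ/H.

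- *Three equal rounds, H = 10.* Complete: n = 30, n/H = 3. One round missed: n = 20, n/H = 2. Ratio 2/3, so the cluster's AI is a third too low.
- *Pooled schedule, 57 visits (see step 2).* One all-house round missed: 47/57 = 0.825, or 17.5% too low. A whole 4-month block missed (10 + 3×3 = 19 visits): 38/57 = 2/3, again a third too low.
- *Same n/H in every cluster.* The two offsets differ by a constant that goes into the intercept, and the arm coefficient does not change.

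The error therefore needs unequal visit counts. It shifts the between-arm ratio systematically if missed visits differ by arm; otherwise it adds between-cluster noise.

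**2. Share of visits from the sentinel houses.** The abstract puts the intervention after 1 year of a 2-year collection. The Interventions section gives a 10–12 month baseline, which leaves M = 12 to 14 months. With R all-house rounds:

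- if a round replaces that month's sentinel visit: 3M of 10R + 3(M − R) visits;
- if all monthly visits are additional: 3M + 3R of 10R + 3M visits.

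| M, R | Coinciding | Additional |
|---|---|---|
| 12, 3 | 36/57 = 63.2% | 45/66 = 68.2% |
| 13, 3 | 39/60 = 65.0% | 48/69 = 69.6% |
| 14, 3 | 42/63 = 66.7% | 51/72 = 70.8% |
| 14, 4 | 42/70 = 60.0% | 54/82 = 65.9% |

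Four rounds within 13 months would give 39/67 = 58.2% or 51/79 = 64.6%. In the sample-size layout any three houses supply 9/30 = 30%. With 57 visits, each sentinel house counts 12/3 = 4 times as much as another house. The effective number of houses, (Σw)²/Σw², is 57²/(3×12² + 7×3²) = 3249/495 = 6.6 instead of 10.

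**3. Precision at the plan's own values.** Inputs from Sample size: mean 0.78, dispersion 2.03, between-cluster CV 0.33, and a 90% difference, read here as a reduction to 0.078. Let s be the share of overdispersion that is a lasting house effect; the article does not give it, so the full range is shown. For one cluster per arm:

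Var(log ratio) = 2×0.33² + A(1/0.78 + 1/0.078) + 2×2.03×[(1 − s)A + sB]

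The first term is 0.218 and the bracket multiplying A is 14.103. A and B are:

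- rounds only: A = 1/30, B = 0.1;
- pooled: A = 1/57, B = 495/3249 = 0.152;
- equal house weights on all 57 visits: A = (7/3 + 3/12)/100 = 0.0258, B = 0.1.

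| s | Rounds only | Pooled | Equal house weights |
|---|---|---|---|
| 0 | 0.823 | 0.536 | 0.687 |
| 0.5 | 0.959 | 0.810 | 0.838 |
| 1 | 1.094 | 1.084 | 0.988 |

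At these values pooling is never less precise than the three rounds. Equal weighting runs from 28% more variance than pooling (0.687/0.536) to 9% less (0.988/1.084).

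**4. The plan's own cluster number.** The two-mean cluster formula with 30 visits per cluster gives 2.92 clusters per arm, not 17. The stated 34 appears with 3 visits per cluster (16.39, rounded up to 17 per arm). That is a separate matter, and nothing above depends on it.

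**The case against.** **The offset is loose wording.** The sentence does name house visits as the exposure. Under Effect of intervention on secondary outcomes, the Breteau index denominator is explained as houses multiplied by time points. The intention is probably visits, and this stands as a reading of intent. The formula as printed is still wrong, and it belongs to the primary model.

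**Pooling does no harm to the comparison.** This stands in large part. A reader might infer three stronger things that the documents do not support:

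- *That pooling biases the between-arm ratio.* Both arms follow the same schedule. The ratio would move only if the effect differed between sentinel and other houses, and nothing in the article suggests that.
- *That the index becomes a measure per sentinel-house visit.* In the 57-visit case, 21 visits (37%) come from the other seven houses. The index is weighted towards the sentinel houses, not confined to them.
- *That pooling loses precision against the three rounds once within-house correlation is moderate.* That needs one common correlation of about 0.23 or more in both arms and ignores between-cluster variance. At a mean of 0.078, extra-Poisson variation is 2.03×0.078/(1 + 2.03×0.078) = 13.7% of the variance, so the correlation there cannot exceed 0.137. Pooling can lose in other scenarios: with an 80% reduction and s = 0.75, the variance is 0.834 pooled against 0.813 for rounds only. That is not the planned case.

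**Rounds only has its own cost.** It leaves about three time points against a 3-monthly larvicide cycle. This is fair, and it is why rounds only is offered as a companion analysis and not as the one correct choice.

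**Weighting is detail for an analysis plan.** It could be, but the article does not leave it open: it fixes the numerator, denominator and aggregation, and its sample size describes a different set of visits.

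**Conclusion.** The offset is specified inconsistently in the primary model and should be corrected. If log(houses) were used, a cluster that lost one of three equal rounds would have its AI understated by a third (17.5% for one round under the 57-visit schedule). With equal visits per house everywhere, the arm effect would not change.

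The primary AI as written also draws about 60 to 71% of its house visits from three of the ten houses, against 30% in the layout assumed for the sample size. The central figure of 63% assumes 12 months, three rounds and coinciding visits. It is a share of visits, not of mosquitoes. The consequence is one of weighting and clarity; neither a biased trial result nor a loss of power has been shown. The precision results rest on the planning values, the same dispersion in both arms, and an unknown split between lasting and passing house variation.

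**What to change.** - Write the offset as log(number of house visits) in the primary model, and carry the same wording to the secondary outcomes that are analysed like the AI, each with its own denominator.
- State which post-intervention visits enter the primary AI.
- Beside the pooled estimate, report one that averages within house and weights the ten houses equally, or one that uses only the all-house rounds.

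The cost is wording and one further analysis; no extra data are needed. The downside is that the companion estimate loses precision if repeat counts within a house are weakly correlated: at s = 0 and the planning values, 28% more variance with equal weights and 53% more with rounds only (0.823/0.536).
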